## Abstract

**Background:**

The lack of adherence to prescribed antihypertensive medication occurs in 50% of patients and leads to poor health outcomes and increased medical costs. Consistent use of antihypertensive medications among patients with hypertension is essential to the reduction of short- and long-term cardiovascular complications. Strategies to improve medication adherence include syncing prescription medications in the pharmacy, which allow patients to retrieve chronically prescribed medications in one visit. The adoption of medication synchronization has been shown to improve adherence to medications; however, there is a lack of data showing if the intervention reduces blood pressure and improves long-term health outcomes.

**Objective:**

This study aims to determine the association between participation in an appointment-based medication synchronization service and blood pressure levels among patients on antihypertensive medications.

**Methods:**

This longitudinal prospective cohort study will observe changes in blood pressure among individuals in a medication synchronization program and those in a usual care group. Patients on at least two antihypertensive medications and four total medications have been recruited to participate in the study. All participants will be required to have at least a 6-month history of filling prescriptions at the pharmacy prior to enrollment in the study. Based on an estimated standard deviation of 14 mmHg, a sample size of 70 participants provides approximately 80% power with a two-sided .05 significance to detect a difference of 9 mmHg blood pressure between the two cohorts.

**Results:**

As of the publication of this paper, patients are completing final blood pressure visits at the pharmacy and medication data are being collected from the pharmacy. Once patients complete all blood pressure visits, data analysis will begin.

**Conclusions:**

This study will link medication synchronization and changes in blood pressure levels among individuals with hypertension. This study will provide preliminary data for a randomized clinical trial that will assess the impact of medication synchronization on blood pressure.

**International Registered Report Identifier (IRRID):**

DERR1-10.2196/12527

## Introduction

### Background

Despite the multitude of treatment options for the management of hypertension, heart disease and stroke remain the leading causes of death attributed in part to high blood pressure. Among the 75 million Americans with hypertension, 74.9% of patients are being treated and only 52.5% of patients are under control [1]. Although effective medications to lower blood pressure have been around for decades, lack of medication adherence occurs among 50% of patients and leads to poor health outcomes [2]. Medication nonadherence is attributed to multiple factors, including lack of health system coordination, asymptomatic disease, patient-specific factors, and complexity of drug regimens [3].

Pharmacy-based strategies to improve medication adherence include the incorporation of synchronization, which enables patients to retrieve multiple medications systematically on one predetermined date [4-6]. Currently, there is limited literature suggesting medication synchronization might improve health outcomes in chronic conditions such as hypertension. One study examined the effect of medication synchronization or an education program on hypertensive health outcomes of patients in a community pharmacy setting [7]. After 4 months of enrollment in medication synchronization, patients achieved an average systolic blood pressure (SBP) reduction of 4 mmHg (*P*=.04) [7]. However, it is important to note that the control and education groups both achieved significant reductions in SBP (9 mmHg, *P*=.001 and 10 mmHg, *P*<.001, respectively) [7]. These significant findings may have been due to the feedback patients received, as all groups had their blood pressure taken and were educated when picking up their medications [7]. A review of participants recruited for the study indicated that baseline blood pressures were low at the start of the study—average baseline SBP of 138 mmHg and diastolic blood pressure (DBP) of 79 mmHg—which may have contributed to a lack of change at the conclusion of the study [7]. Additionally, there was no change in the patients’ reported self-adherence to medications within any groups [7]. This may suggest that ensuring patients have their medications by implementing medication synchronization alone may not be enough to improve patient adherence and, in turn, health outcomes.

Other literature may not specify medication synchronization as the intervention used. Although other studies may not be identically comparable to medication synchronization, there are some similarities to the interventions performed that merit investigation. One such example is the Federal Study of Adherence to Medications in the Elderly (FAME) study, which examined the effect of a pharmacy care program on patient adherence and persistence [8]. This study also examined the pharmaceutical care program’s effect on blood pressure and cholesterol outcomes. The authors found that improved adherence was associated with improvements in SBP, with the pharmaceutical care group achieving greater SBP reduction than usual care (-6.9 mmHg and -1.0 mmHg, respectively, *P*=.04) [8]. The pharmaceutical program consisted of providing medication education, dispensing of medications using blister packaging, and regular follow-up with a pharmacist every 2 months. Individualized education was provided to teach patients about drug names, indications, strengths, adverse effects, and instructions for use during visits [8]. Medication education is commonly performed by pharmacists and can be a component of the medication synchronization intervention along with regular follow-up. Medication synchronization requires pharmacists to go over the medication list with the patient each month. In doing so, regular follow-up occurs and the patient or pharmacist may have questions that lead to medication education or more comprehensive medication therapy management services.

Though there are similarities between medication synchronization and the FAME study intervention, the key difference is the use of blister packaging in the study. Thus, the study cannot directly be compared to a medication synchronization intervention due to the inclusion of compliance packaging. Although medication synchronization has been shown to indirectly improve medication adherence, it is not known if utilization leads to reduced blood pressure. Therefore, we aim to determine the association between participation in a medication synchronization service and blood pressure levels among patients on antihypertensive medications.

The overall objective of this project is to determine the association between participation in an appointment-based medication synchronization service and blood pressure levels among patients on antihypertensive medications. Other study objectives are to examine whether the effect of an appointment-based medication synchronization service on patients’ blood pressure vary based on time-invariant demographic characteristics and time-variant characteristics of the subjects. Data generated from this study will determine the appropriate study size for a larger clinical trial of the intervention.

### Aims and Hypothesis

Aim 1 is to examine the association between enrollment in an appointment-based medication synchronization program and study participants’ blood pressure levels. Hypothesis 1 is as follows: consistent enrollment within a medication synchronization service will be associated with lower blood pressure measurements. This hypothesis will be tested using blood pressure ascertained over a follow-up period of up to 10 months.

Aim 2a is to examine whether the effect of an appointment-based medication synchronization program on patients’ blood pressure varies based on time-invariant demographic characteristics of patients, such as gender, age, education, income, and ethnic origin.

Aim 2b is to examine whether the effect of an appointment-based medication synchronization program on patients’ blood pressure varies based on time-variant characteristics of patients, such as weight, lifestyle change, adverse health behavior, ethanol use, frequency and intensity of exercise, adverse drug reaction, the number of medications, and adherence rates.

Aim 3 is to describe the level of patient satisfaction with enrollment in an appointment-based medication synchronization program.

## Methods

### Study Design

This is a longitudinal prospective study to observe whether enrollment in an appointment-based medication synchronization program will change SBP and DBP levels in patients with hypertension (ie, SBP/DBP of 140/90 mmHg or more) [9]. Two cohorts of patients will be recruited from pharmacy patrons who will volunteer to enroll in the study.

Group 1 (medication synchronization group) comprises patients voluntarily participating in the study and who will enroll in the appointment-based medication synchronization program.

Group 2 (traditional pharmacy medication pick-up group) comprises patients voluntarily participating in the study and who refuse to participate in the appointment-based medication synchronization program.

### Human Subjects

All procedures, informed consent protocols, and study documents were approved by the University of Toledo Biomedical Institutional Review Board. Study procedures were all approved by the pharmacy practice site.

### Informed Consent

All research subjects will sign written informed consent forms prior to participating in the study.

### Study Population

Recruitment will occur among patients that utilize an independent pharmacy for prescription services in Toledo, Ohio. The pharmacy’s computer software will be screened for patients that potentially meet the inclusion criteria (see Figure 1). Up to 100 patients eligible to participate based on inclusion and exclusion criteria will be enrolled in the study. Textbox 1 describes inclusion and exclusion criteria. A flyer describing the study will be posted in the pharmacy to recruit individuals. The flyer will emphasize that participation is voluntary and that a participant may withdraw at any time during the study. The flyer encourages potential participants to call the principal investigator or a coinvestigator if they are interested in learning more about the study. A script was developed that describes the nature of the phone call. Patients interested in the study will be asked to visit the pharmacy to meet with a study investigator who will provide more information about the study. Risks and benefits of the study will be discussed with the patient. If, after meeting in person, the individual is interested in participating in the study, they will be invited to complete the informed consent document. Subjects may withdraw from the study at any time without prejudice to their care.

### Study Procedures

After the baseline clinic visit, patients that meet the study inclusion and exclusion provisions will be followed by cohort depending on the services they decide to utilize in the pharmacy. Participants will be categorized as participating in medication synchronization or traditional medication pick-up group. Participation in any of these pharmacy services are voluntary and are a part of care offered by the pharmacy. Participants will notify investigators as to which cohort they would like to participate in at the month-1 research visit.

The baseline visit procedure includes confirmation that all inclusion and exclusion criteria are satisfied, verification of participant consent and contact information, and completion of baseline data survey, including obtaining blood pressure for analysis. The follow-up visit schedules for data collection do not differ by cohort groups. Table 1 provides more detail about scheduled research visits and information that will be collected. For data collection in both groups, all participants will have visits at months 1, 4, 7, and 10. For event ascertainment, participants in both groups will be queried regarding the occurrence of a possible event on the same schedule, specifically every 3 months. Follow-up in-person visits at the pharmacy will involve gathering of blood pressure data. Follow-up phone call surveys will involve gathering data on changes in health status and satisfaction with pharmacy services.

A multitude of physical measures and medication data will be collected throughout the study via five research pharmacy visits or four phone call surveys. A one-time medical history will be collected at baseline to serve as a screening tool as well as an eligibility and stratification factor. The following physical measures will be collected at baseline: seated blood pressure, weight, height, gender, age, medical history, sociodemographic data, and smoking and alcohol usage. Seated blood pressure, physical measures, and questionnaires will be gathered during pharmacy visits, while all other information, including health status and satisfaction with pharmacy services, will be collected via phone call surveys. Sociodemographic information will reflect age, race, date of diagnosis, ethnicity, gender, level of education, marital status, persons living with participants, and US postal code. This data will be used to identify eligible participants and to characterize the final study population. Baseline medication data include the number of medications, type of medications, and adherence. *Proportion of days covered* will be utilized to assess medication adherence. Monthly medication data will be collected to evaluate prescription records to assess adherence. Seated blood pressure, weight, sociodemographic data, and smoking and alcohol usage will be collected every 3 months starting from the first month of the study.

**Figure 1 figure1:**
[figure not shown]
Study diagram.

List of inclusion and exclusion criteria for study.Inclusion criteria:Subject is an adult, 18 years of age or older.Subject is able to read, understand, and sign a written informed consent form to participate in the study.Subject has systolic blood pressure >140 mmHg or diastolic blood pressure >90 mmHg during the baseline period.Subject has been an established patron of Toledo Family Pharmacy Inc for at least six previous refills of blood pressure medications.Subject has filled more than four prescriptions at Toledo Family Pharmacy each month for the past 3 months.Subject has a history of hypertension and has been prescribed at least two antihypertensive medications.Subject possesses an active phone number where they can be reached.Subject is willing and able to comply with the study protocol.Exclusion criteria:Subject is participating in another clinical trial within four weeks of the baseline period involving an intervention that could affect the outcome measures of this study.Subject has end-stage renal disease and is on dialysis.Subject had a heart attack in the previous six months.Subject had a stroke in the previous six months.Subject is currently enrolled in an auto-delivery program or medication packaging program.Subject has a psychiatric or mental disorder that, in the judgment of the investigator, could interfere with provision of informed consent or completion of survey questionnaires.Patient has a designated power-of-attorney that signs for medications, which renders them not competent to sign the informed consent form.

**Table 1 table1:** Study timeline and data collection.

Data to be collected		Baseline	Month									
			1	2	3	4	5	6	7	8	9	10
**Physical measures**												
	Seated blood pressure	x	x			x			x			x
	Weight	x	x			x			x			x
	Height	x										
**Questionnaires**												
	Gender	x										
	Age	x										
	Medical history	x										
	Sociodemographic data	x	x			x			x			x
	Smoking and alcohol use	x	x			x			x			x
**Medication data**												
	Number of medications	x	x	x	x	x	x	x	x	x	x	x
	Cost of medications	x	x	x	x	x	x	x	x	x	x	x
	Type of medications	x	x	x	x	x	x	x	x	x	x	x
	Adherence	x	x	x	x	x	x	x	x	x	x	x

The pharmacy will supply the research team with medication data on each of the participants enrolled in the study each month. Data provided will include the number of medications, names of medications, costs of medications, the date when the prescription was filled, and the date when the prescription was picked up from the pharmacy. For each drug, the quantity filled, days’ supply, and prescription number will be obtained. Protected health information collected in the study will be maintained on a key code sheet. This code sheet will be locked in the principal investigator’s office at the University of Toledo. A code will be on all data collection forms to refer to each participant in the study. These efforts will maintain research participants’ confidentiality throughout the study. Data collected on data forms will be maintained in a locked cabinet in the principal investigator’s office, separate from the key code sheet. Data collected on code sheets will also be transcribed to electronic format using REDCap provided by the University of Toledo.

### Data Analysis

By assuming a medium effect size of 0.75 times standard deviation for the intervention and set power at 0.8 with a two-sided alpha of .05, the sample size needed is 70 participants, with 35 in each group, allowing for up to 20% attrition. Based on the estimated standard deviation of 14 mmHg, the proposed sample size will provide approximately 80% power to detect a difference as small as 9.5 mmHg between intervention and control groups [7]. Descriptive statistics will be presented as mean (SD) for continuous data and percent frequency (interquartile range) for categorical data to describe patients’ characteristics.

Given the observational nature of the study and patients’ self-selection of the treatment arms, inverse-probability -of-treatment weighted (IPTW) estimation of marginal structural models (MSMs) will be employed in this study. This estimation addresses both sources of potential bias, such as confounders or covariates (eg, age, income, and medication profiles) and missing data under the missing-at-random (MAR) assumption, the most popular informative mechanism in practice. MSMs are a class of statistical models used for causal inference in epidemiology and use a multi-step estimation strategy to control for the effect of confounding variables, allowing the investigator to obtain unbiased estimates [10-12]. Among the several methods that have been proposed to estimate the parameters in MSMs, IPTW is the most commonly used one to address confounding variables [13]. It tries to control for confounding variables by assigning each observation a weight and uses this to create a *pseudo-population,* where treatment arm and control arm are balanced over the confounder [10]. When applied to our study, an MSM consists of three submodules that models the following: (1) the probability of receiving treatment (ie, synchronized arm) for each participant and the weights of the IPTW estimator are simply the inverse of those probabilities; (2) the probability of missing data under MAR and the inverse of those probabilities are used as weights to account for missing values; and (3) the effects of synchronization on blood pressure using reweighted samples. Logit link will be used in both auxiliary modules for the treatment arm and missing data. By controlling for observed confounders and missing data mechanisms through the two auxiliary modules, the main module will provide valid inference about treatment differences in the absence of hidden bias. Statistical significance is set at an alpha of .05 for all analyses.

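### The Abstract's 9 mmHg does not reach 80% power with 70 participants, and the Data Analysis figure of 9.5 mmHg does so only if nobody is lost

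*Protocol article*

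**What the plan says.** The Data Analysis section sizes the study in two consecutive sentences. The first takes a standardised effect, "By assuming a medium effect size of 0.75 times standard deviation for the intervention", with 80% power and a two-sided .05 test, and concludes that "the sample size needed is 70 participants, with 35 in each group, allowing for up to 20% attrition". The second moves to blood pressure units. "Based on the estimated standard deviation of 14 mmHg", it states, "the proposed sample size will provide approximately 80% power to detect a difference as small as 9.5 mmHg between intervention and control groups". It does not say whether this counts participants enrolled or participants analysed.

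The Methods part of the Abstract uses the same SD and says that "a sample size of 70 participants provides approximately 80% power with a two-sided .05 significance to detect a difference of 9 mmHg blood pressure".

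The Study Population section separately allows up to 100 patients to be enrolled. Neither power statement refers to that cap.

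**The concern.** With sample size, SD, test level and power all fixed, a two-group comparison of means has one detectable difference. The article prints two, 9 and 9.5 mmHg, and its sizing effect implies a third: 0.75 × 14 = 10.5 mmHg. At least one printed figure must therefore be wrong, or the figures must rest on different counts that are not named.

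The stake is the stated sensitivity of the study. Someone reading a null result against the Abstract would credit the design with 80% power for 9 mmHg, which it does not have. The article also presents the study as groundwork for sizing a later randomised trial, so its own sizing statement should be one that a reader can reproduce.

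**Working it through.** **Inputs, all from the protocol article**
- Two-sided alpha .05 and power 0.80 (Data Analysis; Abstract)
- Sizing effect 0.75 SD (Data Analysis)
- SD 14 mmHg (Data Analysis; Abstract)
- 70 participants, 35 per group, with up to 20% attrition counted within the 70 (Data Analysis)
- Stated detectable differences: 9.5 mmHg (Data Analysis) and 9 mmHg (Abstract)

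The method is a two-sample comparison of means with equal groups. Each result is given by the normal approximation and by the noncentral t.

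**Step 1. Reproduce the 70**

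n per group = 2(z₀.₉₇₅ + z₀.₈₀)² / δ², with δ in SD units.

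2 × (1.960 + 0.842)² / 0.75² = 27.9, so 28 per group. Allowing for 20% attrition, 28 / 0.8 = 35 per group, or 70 in total. This matches the plan exactly. The 70 enrolled were therefore built on 28 completers per group, 56 in all. (The t version gives 29 per group, which becomes 37 after the same inflation.)

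**Step 2. Put the sizing effect in mmHg**

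0.75 × 14 = 10.5 mmHg. Conversely, 9.5 / 14 = 0.679 SD and 9 / 14 = 0.643 SD.

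**Step 3. Power for each difference on each basis**

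Normal approximation: power ≈ Φ( (Δ/SD) × √(n/2) − 1.960 ).

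Worked example, 9.5 mmHg with 35 per group: 0.679 × √17.5 = 2.839; 2.839 − 1.960 = 0.879; Φ = 0.810.

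| Difference | 35 per group (no attrition): normal / t | 28 per group (20% attrition): normal / t |
|---|---|---|
| 9 mmHg | 76.7% / 75.5% | 67.2% / 65.6% |
| 9.5 mmHg | 81.0% / 79.9% | 71.9% / 70.3% |
| 10.5 mmHg | 88.1% / 87.1% | 80.1% / 78.7% |

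**Step 4. Difference detectable with 80% power**

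Δ = SD × (1.960 + 0.842) × √(2/n).

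- 35 per group: 9.38 mmHg (normal), 9.51 mmHg (t)
- 28 per group: 10.48 mmHg (normal), 10.67 mmHg (t)

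The 9.5 mmHg figure is thus the t-test answer for 35 analysed per group. The 9 mmHg figure matches neither count.

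**Step 5. Enrolment that would support the printed figures after 20% attrition**

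- 9.5 mmHg: 35 / 0.8 = 43.75, rounded up to 44 per group, 88 in total (t: 36 / 0.8 = 45, total 90)
- 9 mmHg: 38 / 0.8 = 47.5, rounded up to 48 per group, 96 in total (t: 39 / 0.8 = 48.75, rounded up to 49, total 98)

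**The case against.** A reader might infer that the 80% power claim is wrong throughout, or that all three differences are incompatible. The article does not support that. The 70 follows exactly from 0.75 SD with 20% attrition, and 9.5 mmHg has 79.9–81.0% power with 35 per group, which is fairly called about 80%. The 10.5 and 9.5 mmHg figures fit together once one is read as 28 completers per group and the other as 35. The 20% is a ceiling, so the 9.5 mmHg figure can be taken as the favourable end of a range. All of this stands, and it limits the fault in the Data Analysis section to an unlabelled change of basis between two sentences.

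It can also be said that 28 per group is a worst case. Blood pressure is taken at baseline and at months 1, 4, 7 and 10, missing data are to be handled by weighting, and a participant who leaves may still contribute earlier readings. That is fair, so 70–72% is the power at the stated attrition limit under a simple two-group comparison, not a forecast.

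The cap of 100 does not rescue the printed claims, because both are tied to 70. If 100 were enrolled, assumed 50 per group and 40 after 20% attrition, power (normal) would be about 82% for 9 mmHg and 86% for 9.5 mmHg, but the article does not argue this.

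A reader might also say that the planned weighting and self-selected group sizes push power lower still. They may, but the article gives no figure from which to size that effect, and use of baseline and repeated readings could work the other way. It is a caveat to state, not part of the error.

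None of these points helps the 9 mmHg figure, which falls short even with full retention.

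**Conclusion.** The point holds in two parts.

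- **Abstract, 9 mmHg:** wrong as written. Power is about 76% with no attrition and about 66–67% at 20% attrition. The figure also contradicts the Data Analysis section on identical inputs.
- **Data Analysis, 9.5 mmHg:** correct only if all 35 per group are analysed, although the preceding sentence counts attrition inside the 70. At 28 completers per group its power is about 70–72%. The difference detectable with 80% power is then 10.5 mmHg (normal; the plan's own 0.75 SD) or 10.7 mmHg (t).

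This rests on the article's SD of 14 mmHg, equal groups and an unweighted two-sample comparison. It does not mean that the sample size was miscalculated, and it does not determine what a null result would rule out. The confidence interval will do that.

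**What to change.** State one detectable difference, on one named basis, in both the Abstract and the Data Analysis section: 70 enrolled, 56 analysed after 20% attrition, about 80% power for about 10.5 mmHg (0.75 SD at an SD of 14 mmHg), before any effect of weighting or unequal group sizes. Remove the 9 mmHg. If 9.5 mmHg is kept, label it as the figure with no attrition.

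The cost is wording only. The stated detectable difference becomes slightly less favourable; no patients are added and no analysis changes.

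### Both weights are defined by the wrong probability, so the weighting as written does not remove self-selection confounding and moves arm means further from the truth when data are missing

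*Protocol article*

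**What the plan says.** The protocol article, Data Analysis, sets out a marginal structural model in three modules.

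- **Treatment module.** It models the "probability of receiving treatment (ie, synchronized arm) for each participant and the weights of the IPTW estimator are simply the inverse" of that probability.
- **Missing-data module.** It models "the probability of missing data under MAR and the inverse of those probabilities are used as weights to account for missing values".
- **Link.** "Logit link will be used in both auxiliary modules for the treatment arm and missing data".
- **Main module.** The effect of synchronization on blood pressure is estimated in the reweighted sample.

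The section also says what the weights are for: a pseudo-population "where treatment arm and control arm are balanced over the confounder". It concludes that "the main module will provide valid inference about treatment differences in the absence of hidden bias". The reason given for weighting at all is "Given the observational nature of the study and patients’ self-selection of the treatment arms". The Discussion again relies on the marginal structural models to deal with self-selection.

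**The concern.** Let p be the modelled probability of choosing synchronization. The parenthesis in the treatment module fixes the modelled probability as that of the synchronized arm, and the weight is its inverse for every participant. The weight 1/p is right for those who synchronize. Those who chose traditional pick-up need 1/(1-p), which appears nowhere in the article.

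The second module inverts the probability of being missing. Only observed records have a blood pressure to analyse, and they need the inverse probability of being observed. With the inverse probability of being missing, the largest weights go to the people least likely to be missing, who are already over-represented.

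The stakes are high because weighting is the only safeguard the article states. Study Design forms Group 2 from patients who refuse synchronization, so the arms may well differ at the start. Per the Discussion, the estimate will also supply the effect size and sample size for a later trial.

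**Working it through.** **The plan's own figure.** The article gives no number for the weights. Its sample size reproduces and does not depend on this point. With a 0.75 SD effect and "set power at 0.8 with a two-sided alpha of .05", n = 2(1.960 + 0.842)²/0.75² = 27.9, so 28 per arm. Then 28/0.8 = 35 per arm, 70 in all.

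**Inputs.** From Data Analysis: SD 14 mmHg, logit link in both modules, attrition up to 20%. Assumed, because the article gives none: one confounder L ~ N(0,1), a logistic slope b of 0.5, and a correlation of 0.5 between L and blood pressure, so 0.5 × 14 = 7 mmHg per SD of L.

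**Treatment weight.** Let p(L) be the probability of synchronization and f(L) the density of L. With 1/p in both arms:

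- synchronized arm: f·p·(1/p) = f, mean of L = 0;
- pick-up arm: f·(1-p)·(1/p) = f·(1-p)/p, proportional to f·exp(-bL), mean of L = -b.

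The imbalance is therefore b. More generally, one function of L multiplies both arms, so the odds of synchronization at each L are unchanged and the confounding remains. With 1/(1-p) in the pick-up arm, both means are 0.

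Imbalance in L between arms, in SD (intercept 0):

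| Slope b | Unweighted | As written | Correct |
|---|---|---|---|
| 0.3 | 0.294 | 0.300 | 0 |
| 0.5 | 0.472 | 0.500 | 0 |
| 1.0 | 0.826 | 1.000 | 0 |

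At slope 0.5 and 7 mmHg per SD, the bias in the difference is 0.472 × 7 = 3.3 mmHg unweighted, 0.500 × 7 = 3.5 mmHg as written, and 0 when correct.

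The direction of change is not general. For a binary L with p = 0.7 when L = 1 and 0.3 when L = 0, the difference in the proportion with L = 1 changes as follows:

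| Prevalence of L = 1 | Unweighted | As written |
|---|---|---|
| 0.2 | 0.272 | 0.156 |
| 0.5 | 0.400 | 0.345 |
| 0.8 | 0.272 | 0.376 |

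**Missing-data weight.** Let m(L) be the probability of being missing. Observed records weighted by 1/m have density f·(1-m)/m, again proportional to f·exp(-bL), so the mean of L moves to -b. At 20% missing (true mean 0):

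| Slope b | Unweighted | As written | Correct |
|---|---|---|---|
| 0.3 | -0.059 | -0.300 | 0 |
| 0.5 | -0.096 | -0.500 | 0 |
| 1.0 | -0.173 | -1.000 | 0 |

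At slope 0.5 the bias in a mean is -0.096 × 7 = -0.7 mmHg for complete cases and -0.500 × 7 = -3.5 mmHg as written. The distortion grew in every case run, binary L included.

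**From means to the between-arm difference.** Suppose the treatment weights are correct and the logit of missingness is additive in L and arm. The tilt exp(-bL) is then the same in both arms and cancels from the difference if the effect is constant. It does not cancel in two situations:

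- the effect varies with L: at b = 0.5, each 1 mmHg per SD of effect modification moves the difference by 0.5 × 1 = 0.5 mmHg;
- the missingness slope differs by arm: slopes of 0.5 and 0 shift the difference by 7 × 0.5 = 3.5 mmHg.

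**Simulation.** 2,000,000 records, true effect -5 mmHg, blood pressure 5 mmHg lower per SD of L, treatment slope 0.5, missingness depending on L and arm:

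| Analysis | Full data | Observed records |
|---|---|---|
| Unweighted | -7.36 | -7.15 |
| As written (on observed records, both weights) | -7.49 | -7.52 |
| Correct (on observed records, both weights) | -5.01 | -5.02 |
| Correct treatment weight, missing-data weight as written | not applicable | -5.04 |

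The last row shows the cancellation under a constant effect.

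**The case against.** The strongest reply is that this is loose shorthand. The method named, inverse-probability-of-treatment weighting of a marginal structural model, already means the inverse probability of the treatment received. The section states the goal of balance and cites methodological sources. Modelling missing or observed is one logistic regression with the sign reversed, and the text is a journal article that condenses a fuller document. An analyst who implements the named method to its stated goal would use 1/p and 1/(1-p). That is plausible, and nothing shown proves that the analysis will be programmed as written. But the article does not merely leave the formulas out. It states two rules, both give a wrong result, and nothing elsewhere in it corrects them.

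A reader might infer that both weights increase the bias they are meant to remove. The documents do not support that for the treatment weight: the binary cases go both ways, and in the normal case the rise is only from 3.3 to 3.5 mmHg. A reader might also take the -3.5 mmHg from missing data as bias in the Aim 1 contrast. It is bias in a mean, and it largely cancels when the effect is constant and missingness is additive in covariate and arm.

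It is also fair to say that stabilized weights and bootstrap standard errors are separate choices. They do not follow from this error.

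**Conclusion.** Wrong as written. Followed literally, the treatment weight leaves confounding by self-selection in place. The remaining imbalance may be larger or smaller than with no weighting. Under the stated assumptions the bias is about 3.5 mmHg, over a third of the 9.5 mmHg difference in the power statement (3.5/9.5 = 0.37).

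The missing-data weight moves arm means further from the truth. It harms the between-arm contrast if the effect varies with the covariate, which is what Aims 2a and 2b examine, or if missingness depends on the covariate differently by arm.

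Both rules conflict with the section's own aim of balanced arms and its claim of valid inference. The algebraic conclusion that 1/p in both arms leaves confounding in place needs no assumed values. The sizes in mmHg rest on an assumed normal confounder, slope, correlation and missing rate; only the SD of 14 mmHg and the 20% attrition ceiling come from the plan.

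**What to change.** Replace the two weight definitions in Data Analysis:

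1. The treatment weight is the inverse of the modelled probability of the cohort the participant actually joined: 1/p for synchronization and 1/(1-p) for traditional pick-up.
2. The missing-data weight is the inverse of the modelled probability that the blood pressure is observed, applied to observed records. The analysis weight is the product of the two.

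The cost is two sentences. Data collection, the sample size of 70 and the named method are unaffected. The Abstract says that analysis starts only after all blood pressure visits are complete, so the correction can be made before any result is computed. If the full protocol or analysis plan already defines the weights this way, it is enough to confirm that and correct the article's wording.
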